### Objectives

This protocol outlines a pragmatic, mixed-methods embedded single-case study with a nested within-group pre-post comparison of health outcomes, guided by Pawson and Tilley’s realist evaluation principles [33], to elicit a context-focused and mechanism-driven understanding of outcomes derived from the use of Ned by patients, caregivers, and clinicians within a public hospital network in Toronto, Canada. The aims of this study are 2-fold: (1) to gain an understanding of how a prostate cancer survivorship app called Ned for viewing laboratory results and collecting patient-reported outcomes is adopted and accepted by patients, caregivers, and clinicians; and (2) to determine the effect of Ned on health-related quality of life, satisfaction with cancer care, unmet needs, self-efficacy, and prostate cancer-related levels of anxiety.

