#### Effectiveness of Ned

While a substantial amount of research has been done to address the functional impairments caused by prostate cancer treatments, less emphasis has been placed on alleviating the psychological and emotional barriers faced by survivors throughout their survivorship experience. There is recognition that, while overall satisfaction with prostate cancer follow-up care is high, the presence of problematic treatment-related side effects is associated with higher psychological morbidity, poorer self-efficacy, greater unmet needs, and poorer overall health status [49]. Strategies for identifying those men with ongoing problems, alongside new interventions and models of care tailored to individual needs, are needed to improve quality of life. Novel solutions have been devised, notably the successful implementation of a real-time dashboard platform to integrate prostate cancer-specific PROMs into clinical settings that resulted in higher patient quality of life and satisfaction with care [10]. We are encouraged by this work and seek to explore whether our own technology, which combines the collection of PROMs with the provision of PSA values, can achieve similar outcomes. To establish the degree to which Ned can significantly improve how prostate cancer survivors experience their care, we chose to investigate the app’s impact on 5 specific clinical outcomes: health-related quality of life, satisfaction with cancer care, unmet needs, self-efficacy, and prostate cancer-related level of anxiety. We have operationalized our outcomes using a collection of existing validated questionnaires that have been widely used in prostate cancer survivorship research to standardize our work and facilitate future meta-analyses [50]. We have also selected a data collection schedule matching that of the largest prostate cancer survivorship study ever conducted to enable the comparison of any generated data trends with existing population baseline data [8]. In addition to collecting outcomes data, we will also review patient charts to collect the following clinical variables: Gleason score, cancer stage, treatment group (ie, active surveillance, postsurgery, castration resistant, postradiation, postsalvage radiation, and hormone sensitive), and comorbidities. Table 2 lists the data collection schedule for all outcome measures.

**Table 2 table2:** Data collection schedule for outcomes measures.

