### Sample Size

The appropriate sample size for single-case research depends on the specific research question being investigated and cannot be calculated in the same way as group designs such as the randomized controlled trial. In his seminal writing on case study designs, Yin recommends abandoning traditional sampling logic in favor of reflecting on the number of replications that are desired to maximize both certainty of research findings and external validity [59]. However, we recognize that our study design diverges from traditional case study methodology in nesting a within-group pre-post comparison of health outcomes aimed at identifying possible parameters of clinical change from baseline to study conclusion. We have therefore diverged from Yin’s recommendations and performed a sample size calculation powered to detect a minimal clinically important difference (MCID) of 4 with a standard deviation of 22.25 on the EPIC-26. We selected the most conservative MCID and the median standard deviation from the range of validated values (MCID range 4-12, SD range 12.6-31.9), which have been widely used in prostate cancer survivorship research [60]. With 90% power, an effect size of Cohen *d*=0.16, and a 2-sided significance level of 5%, a minimum of 317 participants are required to detect this MCID. We anticipate a dropout rate of 20%, bringing our total sample size to 400 prostate cancer survivors for recruitment. We performed this calculation using the G*Power 3.1 software [61]. We will actively recruit the 400 patients required to power our within-group pre-post comparison of health outcomes, but we do not have a predetermined sample size for caregivers and clinicians. We anticipate that 10 clinicians will accept the invitation to join the Ned study and 50% of patients will share Ned with their caregivers. This will result in a total study sample size of 610 participants, composed of 400 patients, 200 caregivers, and 10 clinicians.

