#### Quantitative Survey Data

Descriptive statistics will first be conducted on all variables to identify methodological data trends and parameters. We will analyze differences in baseline demographic and clinical variables using Pearson chi-square and nonparametric Wilcoxon rank sum tests. Given that we will be asking the same patients to complete repeated outcome measures across 4 time periods, we will account for autocorrelation effects through the use of linear generalized estimating equations, which are a multivariate analog of linear regression for longitudinal data and recommended for use in longitudinal repeated-measures data analyses [65,66]. Our data analysis strategy to answer the following questions is as follows:

(1) What is the effect of Ned on health-related outcomes over time? To assess the effect of Ned on quality of life, satisfaction with cancer care, unmet needs, self-efficacy, and prostate cancer-related level of anxiety domains, we will use generalized estimating equation models containing indicators for each study time point to assess whether the average study assessment scores at 2 months, 6 months, and 12 months were significantly different from baseline values.

(2) Is there a relationship between patient engagement with Ned and changes in health-related outcomes over time? We will explore whether patients who engage with the content and functionality of the app experience improvements in their health and well-being by building linear regression models for use and outcomes data.

(3) Is there a relationship between health-related outcomes? To understand whether changes in health-related outcomes share a similar direction and magnitude, we will perform Pearson correlation analyses to test for a correlational relationship between outcome variables.

(4) Do demographic and clinical variables affect changes in health-related outcomes? We will first conduct independent *t* tests and 1-way independent analyses of variance to determine whether there were differences in health-related outcomes for all categorical demographic and clinical variables, and Pearson correlation analyses for all continuous variables. We will then perform multiple linear regression analyses with health-related outcomes as dependent variables and all significant predictor variables from our preliminary analyses as independent variables.

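### Four outcomes with no sample-size basis are tested for significance at three visits on the same footing as the EPIC-26, and neither outcomes nor visits are ranked

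*Protocol article*

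**What the plan says.** The second aim in the Objectives section is "to determine the effect of Ned on health-related quality of life, satisfaction with cancer care, unmet needs, self-efficacy, and prostate cancer-related levels of anxiety". The five outcomes stand in one list with no order among them.

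The section Effectiveness of Ned repeats the list and gives its purpose: "To establish the degree to which Ned can significantly improve how prostate cancer survivors experience their care".

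Question 1 under Quantitative Survey Data, which concerns the effect of Ned on health outcomes over time, applies generalized estimating equation models with time-point indicators to all five, "to assess whether the average study assessment scores at 2 months, 6 months, and 12 months were significantly different from baseline values". Table 2 confirms that the measures of satisfaction, unmet needs, self-efficacy and anxiety are each collected at baseline and at all three later visits.

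The Sample Size section treats one instrument differently. The authors "performed a sample size calculation powered to detect a minimal clinically important difference (MCID) of 4 with a standard deviation of 22.25 on the EPIC-26", for change between baseline and the end of the study, with "a 2-sided significance level of 5%, a minimum of 317 participants are required to detect this MCID". No difference, power or rank is given for the other four outcomes.

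Adoption is called a core outcome in its own section, but that does not rank the five health outcomes against each other.

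**The concern.** Which outcome and visit decide an aim is a protocol-level choice. Here the text does describe the testing scheme: five co-equal outcomes, each judged significant or not at three visits, under a question about the app's effect. The sizing logic rests on one instrument and points to one contrast, but the analysis does not carry that priority through.

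The cost falls on interpretation. With at least 12 comparisons on unpowered outcomes, some nominal significance by chance is a substantial possibility even if the app changes nothing. If outcomes disagree, for example if satisfaction rises while anxiety worsens, the article does not say which bears most on the second aim. Emphasis could then be chosen after the results are seen.

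**Working it through.** **1. The plan's own figure.** Inputs from the Sample Size section: difference 4, SD 22.25, 90% power, two-sided 5%, 20% dropout. For a paired mean, n = ((z₀.₉₇₅ + z₀.₉₀)/d)².

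- With d = 4/22.25 = 0.180: ((1.960 + 1.282)/0.180)² ≈ 325.1, so 326. This is within 3% of the stated 317.
- Dropout: 317/0.8 = 396.25, so 397, consistent with 400.
- The printed effect size of 0.16 does not equal 4/22.25 and would give 411. That is a separate matter and has no bearing on what follows.

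The 5% level therefore belongs to a single EPIC-26 comparison.

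**2. Number of tests on the four unpowered outcomes.**

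- One score each at 2, 6 and 12 months: 4 × 3 = 12.
- Scores as the measure descriptions give them: satisfaction 1, unmet needs 5 domains, self-efficacy 1, anxiety 3 subscales. That is 10 scores, and 10 × 3 = 30 tests.
- One score each at 12 months only: 4.

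Question 1 uses the word *domains* at the end of its outcome list. This allows the 30-test reading but does not settle it.

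**3. Chance of at least one |z| > 1.96 when no mean changes.** Under independence this is 1 − 0.95^k:

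- k = 4: 18.5%
- k = 12: 46.0%
- k = 30: 78.5%

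The tests will be correlated, and the article gives no correlations, so they are assumed. A between-visit value of 0.5 is a natural centre. For changes from a shared baseline with equal variances and equal correlations ρ, the covariance is σ²(1 − ρ) and each variance is 2σ²(1 − ρ), so the ratio is 0.5. Simulation of multivariate normal z statistics, with correlation equal to the between-outcome value times the between-visit value, gives for 12 tests:

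| Between visits | Between outcomes 0 | 0.3 | 0.5 | 0.8 |
|---|---|---|---|---|
| 0 | 46% | 44% | 40% | 31% |
| 0.5 | 41% | 39% | 36% | 27% |
| 0.7 | 37% | 35% | 31% | 23.5% |

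For 30 tests:

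| Between visits | Between outcomes 0 | 0.3 | 0.5 | 0.8 |
|---|---|---|---|---|
| 0 | 79% | 73% | 64% | 43% |
| 0.5 | 74% | 68% | 59% | 38% |
| 0.7 | 69% | 62% | 53% | 34% |

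For 12 months only, one score each (4 tests), the range is 11% (between-outcome correlation 0.8) to 19% (correlation 0).

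**4. Reading.** With one score per outcome the chance is well above 5% but below even odds in every setting. With domains and subscales tested separately it exceeds 50% at between-outcome correlations up to 0.5, but not at 0.8.

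**The case against.** The strongest reply is that this is a realist case study and not a confirmatory trial. The Introduction says the evaluation does not ask simply whether the app works. Effectiveness of Ned speaks of exploring whether earlier results can be matched. Trial Design and Sample Size speak of parameters of possible clinical change, and the results are to be triangulated with qualitative data. If each outcome is its own question, a family-wise rate is not automatically the relevant one. An alpha adjustment could also sit in an analysis plan that is not shown.

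Much of this stands, and it rules out several stronger readings that a reader might infer:

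- *Any one significant result establishes an effect of the app.* No section states such a rule or a pass/fail verdict on the second aim.
- *The plan breaches its own 5% error rate.* The 5% is attached to the EPIC-26 calculation; no family-wise 5% is claimed.
- *A chance finding is more likely than not.* That holds only for separate domain and subscale testing, and not at every correlation.
- *A multiplicity adjustment is missing.* That detail may properly be elsewhere.
- *Disagreement between outcomes is ignored.* Question 3 examines whether changes agree in direction and size, though it does not rank the outcomes.

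The reply does not remove the point. Trial Design calls the aims both observational and experimental. Sample Size departs from case-study sampling logic in order to power a comparison. Effectiveness of Ned and question 1 use the language of significance, and question 1, unlike question 2, is not worded as exploration. The framing is mixed, and the article gives the reader no ranking to resolve it.

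**Conclusion.** The point holds in a limited form. The article sets out a testing scheme in which four unpowered outcomes stand level with the powered one at three visits, and it ranks neither outcomes nor visits. If no mean changes, the probability of at least one nominally significant result among those four is roughly 23% to 46% with one score each. This assumes two-sided 5% per test, normal statistics, between-visit correlation 0 to 0.7 and between-outcome correlation 0 to 0.8. Separate domain and subscale testing would give about 34% to 79% over the same grid. The missing ranking reaches the EPIC-26 too: it has five domains, and the Sample Size section names none of them. The matter is worth correcting, but it does not invalidate the design.

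**What to change.** In question 1 of Quantitative Survey Data:

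- Name one EPIC-26 score at 12 months as the primary test of the second aim, at two-sided 5%. This follows the baseline-to-end contrast already used for sizing, but the score must be chosen explicitly.
- Label satisfaction, unmet needs, self-efficacy and anxiety as secondary.
- Label the 2- and 6-month contrasts and the subscales as exploratory, reported as estimates with 95% confidence intervals.

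In Effectiveness of Ned, restrict confirmatory language about significant improvement to the primary contrast. Extend it to secondary outcomes only if an adjustment is specified. Holm across the four at 12 months is one option among several; the smallest of the four p-values would then have to fall below 0.05/4 = 0.0125. That option also needs one score per outcome. The article describes unmet needs and anxiety only by domain or subscale, so a summary score would have to be defined for each.

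No new data or patients are needed. The article reports recruitment still under way and completion expected in May 2019, so the ranking could be fixed before outcomes are analysed. The downside is small: some secondary, subscale or early-visit results could no longer be presented as confirmatory.

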### Trial Design

The Ned case study is a 12-month mixed-methods embedded single-case study with a nested within-group pre-post comparison of health outcomes. We will evaluate the adoption, acceptability, and effectiveness of Ned as perceived by the 400 patients, 200 caregivers, and 10 clinicians who are given access to the app. Our aims are both observational and experimental: we are interested in deriving a deep understanding of how Ned affects survivorship care, but also in establishing parameters of possible clinical change to inform the effect of the app on quality-of-life outcomes. We also seek to identify the process mechanisms required to introduce Ned into a public health network, specifically the resources required to support the platform. This knowledge will inform future innovation diffusion efforts for Ned as we look to scale the platform across Canada. We will employ a combination of semistructured interviews, questionnaires, and qualitative observations to illustrate a rich picture of how Ned is adopted, whether it is accepted, and the effect it has on how prostate cancer survivors and their care team experience survivorship care. We have obtained REB approval from the Trillium Health Partners (THP) hospital network for this research (THP REB ID#826). Table 1 outlines the multiple embedded units of analyses planned for this study.

**Table 1 table1:** Summary of embedded units of analyses for the evaluation of the Ned app.

Embedded unit of analysis	Data sources
Patient, caregiver, and clinician adoption of Ned	Analytics log data on the number of patients, caregivers, and clinicians who are invited to open a Ned account, and the consequent number of Ned accounts created
Patient acceptance of Ned	Analytics log data on the frequency, duration, depth, and breadth of patient engagement with the app
	Interviews with 20 patients poststudy
	Web-based questionnaire assessing acceptability
	Qualitative observation of patients using Ned to access prostate-specific antigen results and submit patient-reported outcome measures
Caregiver acceptance of Ned	Analytics log data on the frequency, duration, depth, and breadth of caregiver engagement with the app
	Interviews with 10 caregivers poststudy
Clinician acceptance of Ned	Analytics log data on the frequency, duration, depth, and breadth of clinician engagement with the app
	Wed-based questionnaire assessing system use to be completed by 10 clinicians

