### Eligibility Criteria

Patients must meet the following eligibility criteria to be enrolled into the study: (1) 18 years of age or older, (2) receiving care at the THP Mississauga Hospital or Credit Valley Hospital, (3) pathology report confirming prostate cancer diagnosis via transrectal, transperineal, or transurethral biopsy (standard 12-core template), (4) life expectancy more than 1 year, (5) no concomitant cancer diagnosis, (6) own a device that is compatible with the Ned app and is Web enabled through a data plan or Wi-Fi capabilities, or both (eg, laptop, desktop, tablet, smartphone), (7) able to read, write, and speak English.

Clinicians (ie, urologists, surgical oncologists, radiation oncologists) who are employed by the THP hospital group, practice at either the Mississauga Hospital or Credit Valley Hospital, and are involved in the care of patients with a diagnosis of prostate cancer are eligible to participate in this study; our research group has secured Privacy Impact Assessment and Threat Risk Assessment agreements with both hospitals. Caregivers must be paired with a patient who is enrolled in the study to be eligible for access to Ned. We broadly define caregivers here as a spouse, relative, friend, or formal caregiver of the patient who significantly contributes to their care.

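### Aim 2 and Question 1 call an uncontrolled change from baseline an effect of Ned, and the listed data do not include the treatment timing needed to put that change in context

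*Protocol article*

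**What the plan says.** All references are to the protocol article.

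- **Aim.** The second aim under Objectives is "to determine the effect of Ned on health-related quality of life, satisfaction with cancer care, unmet needs, self-efficacy, and prostate cancer-related levels of anxiety".
- **Design.** Trial Design describes a "nested within-group pre-post comparison of health outcomes", with no concurrent comparator.
- **Analysis.** Quantitative Survey Data, question (1), asks "What is the effect of Ned on health-related outcomes over time". It answers with "generalized estimating equation models containing indicators for each study time point", used to assess "whether the average study assessment scores at 2 months, 6 months, and 12 months were significantly different from baseline values". No covariate is named for this model.
- **Who enters.** Eligibility Criteria require a "pathology report confirming prostate cancer diagnosis via transrectal, transperineal, or transurethral biopsy", with no condition on treatment received or on time since diagnosis or treatment.
- **What is recorded.** Effectiveness of Ned lists the chart variables as "Gleason score, cancer stage, treatment group (ie, active surveillance, postsurgery, castration resistant, postradiation, postsalvage radiation, and hormone sensitive), and comorbidities". Table 2 marks the chart review at baseline only.
- **The instrument.** Health-Related Quality of Life says EPIC-26 serves to assess both prostate-specific quality of life and how function recovers following treatment. It is also the instrument used for the sample size.

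**The concern.** In a single-arm model with visit indicators only, each visit coefficient is the total mean change since baseline, whatever caused it. Candidate causes in this cohort include the app, recovery from treatment given shortly before enrolment, decline after treatment begun during the year, and progression. The protocol itself says its main instrument tracks recovery after treatment, and it admits men at any interval from treatment. Yet it gives the whole coefficient the name of the intervention.

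The listed data offer little help in telling these causes apart. A man coded as postsurgery may be one month or ten years from his operation, and a man on active surveillance at baseline may be treated by month 6 without any scheduled field recording it. At stake is the reading of the main quantitative result in both directions: recovery could look like benefit, and new treatment could hide one.

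**Working it through.** **Inputs from Sample Size.** MCID 4 points on EPIC-26; SD 22.25, taken from a range of 12.6 to 31.9; power 90%; two-sided 5%; minimum 317 analysed; "We anticipate a dropout rate of 20%, bringing our total sample size to 400 prostate cancer survivors for recruitment". Completers expected: 400 × 0.80 = 320.

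**Step 1: the plan's own figure.** For a one-sample (paired) comparison, n = ((1.960 + 1.282) × SD / δ)².
- With δ/SD = 4/22.25 = 0.180, n = 326 (normal) or 328 (t). Power at 317 is 89.1%, so the stated 317 is approximately reproduced if 22.25 is used as the SD of the change.
- The stated Cohen d of 0.16 does not reproduce it: n would be 411 (normal) or 413 (t). That discrepancy is a separate matter, but it is why a range of SDs is shown below.

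**Step 2: smallest mean change that is significant.** Standard error = 22.25/√320 = 1.244. Threshold = 1.967 × 1.244 = 2.45 points.

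**Step 3: how often drift alone is declared an effect.** Suppose the app does nothing and the cohort mean drifts by a fixed amount for other reasons. The chance of a significant result is the power of the same test against that drift (non-central t, n = 320). The drift sizes are assumptions; the article gives none.

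| SD of change (assumed) | Threshold | Drift 2 | Drift 3 | Drift 4 | Drift 6 |
|---|---|---|---|---|---|
| 12.6 | 1.39 | 81% | 99% | >99% | >99% |
| 22.25 | 2.45 | 36% | 67% | 89% | >99% |
| 25 (4/0.16) | 2.75 | 30% | 57% | 81% | 99% |
| 31.9 | 3.51 | 20% | 39% | 61% | 92% |

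By design, a study sized to detect 4 points detects a 4-point change about 90% of the time, whatever its source.

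**Step 4: does anything else planned change the Question 1 estimate?**
- Question 2 regresses outcomes on use. It is also uncontrolled, and it is a different quantity.
- Question 4 relates outcomes to the demographic and clinical variables. It is a separate analysis and leaves the Question 1 coefficients as they are.
- Effectiveness of Ned says the schedule was matched to a large survivorship study so that trends can be compared with population data. That comparison is not part of Question 1. Without a treatment date, treated men could not be aligned with an external cohort by time since treatment.

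**The case against.** The strongest reply is that the uncontrolled design is declared and reasoned. The article explicitly declines to ask simply whether Ned works. Trial Design and Sample Size speak more cautiously of possible clinical change, and the findings are to be triangulated with qualitative data. On this view the point is one of wording. Much of this stands: a pre-post design is legitimate for describing change, and no control arm is asked for. But the cautious wording conflicts with aim 2 and Question 1, which are causal, and none of the mitigations enters the Question 1 estimate.

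It is also fair that the article may not list every item collected. The demographic questionnaire is not shown. The claim is only that treatment date and later treatment are absent from the listed variables and schedule.

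Several stronger readings are tempting but not supported:

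- *Background change will be credited to the app.* The documents show that it cannot be separated from an app effect, not that it will be large or in one direction. Assumed drifts can offset each other. If 20 to 30% of men recovered 12 points (+2.4 to +3.6) and 10% lost 30 points (−3.0), the net would be −0.6 to +0.6, below the threshold.
- *Time since treatment is the main determinant of the EPIC-26 course, and is lost for good if not collected now.* The article does not rank determinants, and the team has chart access, so a treatment date could plausibly be extracted later.
- *Drop-out of 20% will bias the GEE.* That depends on whether loss is related to outcome, on the working correlation and on missing-data handling. The article fixes none of these, and they may be set in an analysis plan not shown. The point does not rely on it.
- *Adding covariates would rescue the causal claim.* Without a comparator they reduce confounding but cannot remove it.

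**Conclusion.** The concern holds in this form. Aim 2 and Question 1 attach a causal label to the mean change from baseline in one uncontrolled, clinically mixed cohort, and the listed data lack the two timing variables that would make the change interpretable by clinical course. Followed as written, the plan would report background change as an effect of Ned whenever it exceeded about 2.45 points. A drift equal to the MCID would do so about 90% of the time with no app effect (61% to over 99% across the protocol's SD range).

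These figures assume 320 completers, the quoted SD as the SD of change (the article says only that it is an SD on EPIC-26), and drift sizes chosen for illustration. The numbers concern EPIC-26. The attribution problem applies equally to satisfaction, unmet needs, self-efficacy and anxiety, because the model is the same, but no size is claimed for those outcomes.

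**What to change.** 1. **Wording.** Restate aim 2 and Question 1 as *change from baseline during use of Ned*, and state that no causal conclusion will be drawn from the visit coefficients alone. This is the only step that addresses attribution directly.
2. **Data.** Add the date of the most recent treatment to the chart review already planned. Add one item to the 2-, 6- and 12-month questionnaires: treatment started or changed since the last assessment.
3. **Analysis.** Report Question 1 change by treatment group (treatment group by time). Use time since treatment as a covariate among treated men only, and keep active-surveillance men as their own stratum because the variable is undefined for them. Add a sensitivity analysis that accounts for treatment changes during follow-up. State that this reduces confounding without removing it.

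The cost is one chart field, one questionnaire item and revised text, with no extra patients or arm. The price in results is a more modest claim and wider intervals within treatment groups.

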Clinical effectiveness of Ned	Five validated patient-reported outcome measures (ie, quality of life, treatment satisfaction, unmet needs, self-efficacy, anxiety) administered at baseline, 2 months, 6 months, and 12 months

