Measure	Data collection method	n	Baseline	2 months	6 months	12 months
Use data	Log data analytics software	610	Throughout study duration			
Demographic data	Web-based questionnaire	400	x			
Clinical data	Chart review	400	x			
Credibility/Expectancy questionnaire	Web-based questionnaire	400	x			
Expanded Prostate Cancer Composite	Web-based questionnaire	400	x	x	x	x
Prostate Cancer-Related Quality of Life Scales	Web-based questionnaire	400	x			
Service Satisfaction Scale for Cancer Care	Web-based questionnaire	400	x	x	x	x
Supportive Care Needs Survey	Web-based questionnaire	400	x	x	x	x
Self-Efficacy for Managing Chronic Disease Scale	Web-based questionnaire	400	x	x	x	x
Memorial Anxiety Scale for Prostate Cancer	Web-based questionnaire	400	x	x	x	x
Modified UTAUT^a^ survey	Web-based questionnaire	400				x
Patient qualitative interviews	(1) Semistructured live interview (2) Qualitative observation of app use	20				x
Caregiver qualitative interviews	Semistructured live interview	10				x
Clinician System and Use Assessment Survey	Web-based questionnaire	10				x

^a^UTAUT: unified theory of acceptance and use of technology.

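### Question 2 regresses outcome change on self-selected app use, with no adjustment named and no rule that use come first, so prior or evolving health, or belief in Ned, can look like an effect of engagement.

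*Protocol article*

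**What the plan says.** The article's Quantitative Survey Data section lists four questions and gives a method for each. Question 2 asks: "Is there a relationship between patient engagement with Ned and changes in health-related outcomes over time". The method sentence begins "We will explore whether patients who engage with the content and functionality of the app" and ends "experience improvements in their health and well-being by building linear regression models for use and outcomes data". It names two inputs, use and outcomes. It names no covariate, no window for use and no time order.

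Use is described in Table 1 (Trial Design) as "Analytics log data on the frequency, duration, depth, and breadth of patient engagement with the app". Table 2 gives its collection period as "Throughout study duration". The five outcome measures are "administered at baseline, 2 months, 6 months, and 12 months". Under Patient Recruitment, the baseline questionnaires are completed before the patient's Ned account is opened, so the baseline score precedes all use.

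The other questions are described more fully. The section says that "we will account for autocorrelation effects through the use of linear generalized estimating equations", and question 1 repeats this with indicators for each time point. Question 4 uses multiple regression with "all significant predictor variables from our preliminary analyses as independent variables". Question 2 has neither.

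**The concern.** Engagement is an exposure that patients choose after baseline, and the article itself gives reasons why it may be tied to outcome:

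- **Belief.** Acceptability of Ned makes baseline credibility and expectancy a predictor of use behaviour. It then says that such belief strongly affects treatment outcomes in chronic conditions. One baseline variable is thus expected to drive both sides of the regression.
- **Disease state.** The treatment groups run from active surveillance to castration-resistant disease (Effectiveness of Ned). These groups plausibly differ in symptoms, course and frequency of PSA testing, and viewing PSA results is a core use of the app.
- **Health during follow-up.** Outlying in-app scores alert the clinician (Intervention), so a change in health may itself alter use.

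The study has no control group. A dose-response between use and improvement would be attractive evidence, and it would feed the program theory built from the quantitative and qualitative data.

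**Working it through.** The article gives no effect size, sample size or power for question 2, so there is no stated figure to reproduce. The check asks how large a spurious association can be when use has no effect.

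**Inputs from the article (Sample Size).** 400 patients and 20% dropout give 400 × 0.8 = 320 completers. The EPIC-26 SD is 22.25 and the minimal important difference is 4. Higher EPIC-26 scores are better.

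**Inputs assumed.** Correlation of use with the baseline score, c = 0.2 to 0.3. Correlation of baseline with 12 months, ρ = 0.5, varied below. Equal SDs at both times. Use depends on health only through baseline.

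**Step 1: correlation of use with change.** With no effect of use, corr(use, Y12) = ρc, so

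corr(use, Y12 − Y0) = (ρc − c) / √(2(1 − ρ)).

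- c = 0.2: (0.10 − 0.20) / √1 = -0.10
- c = 0.3: (0.15 − 0.30) / √1 = -0.15

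The SD of change is 22.25 × √(2 × 0.5) = 22.25. The slopes are therefore about -2.2 and -3.3 points per SD of use, against a minimal important difference of 4. If men in worse health use the app more (c negative), the signs reverse and engagement looks beneficial.

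**Step 2: how often this is declared significant.** Fisher z at n = 320, two-sided 5%: rate ≈ Φ(atanh|r| × √317 − 1.96).

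- |r| = 0.10: Φ(1.787 − 1.96) = 0.43
- |r| = 0.15: Φ(2.691 − 1.96) = 0.77

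**Step 3: sensitivity to ρ.** The formula in step 1 simplifies to -c√((1 − ρ)/2).

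| ρ | c = 0.2 | c = 0.3 |
|---|---|---|
| 0.5 | r = -0.10, 43% | r = -0.15, 77% |
| 0.6 | r = -0.089, 36% | r = -0.134, 67% |
| 0.8 | r = -0.063, 20% | r = -0.095, 40% |

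A simulation at ρ = 0.6 (n = 320, 2,000 replicates) agreed: 36% and 67%, with biases of -1.8 and -2.7 points per SD of use. At c = 0.1 it gave 13% and -0.9 points.

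**Step 4: adjustment for baseline.** The numerator of the partial correlation is ρc − ρ × c = 0. The simulated false-positive rate was about 5%.

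**Step 5: use that follows the health course.** In the same simulation, use was unrelated to baseline but correlated 0.1 or 0.2 with the part of the 12-month score not explained by baseline. The baseline-adjusted model was then biased by +1.8 or +3.6 points, with 44% or 95% false positives. The change-score model gave +1.8 or +3.5 points, with 37% or 88%. Baseline adjustment does not help here, so the timing of use matters as well.

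**The case against.** The strongest reply is that this is a condensed article. Use windows, lags and covariates are commonly left to the full plan, the wording is exploratory, and it asks about a relationship. A linear regression does not exclude covariates, and the relevant variables are collected. Much of this stands. Missing detail alone would be no finding, and the full plan may already supply it. What remains is that the article does state a method for question 2, names predictors for question 4 but none here, and words the result as improvement among those who engage. Calling an analysis exploratory does not remove its bias.

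Some stronger readings are tempting but are not supported:

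- A reader might infer that the baseline outcome is ignored. Question 2 concerns change, so baseline enters through the difference. The defect is that a change score does not remove a baseline imbalance related to use. Figures for a regression of the raw 12-month score on use do not describe this question.
- A reader might infer that use is totalled over the whole study. Table 2 gives the logging period, not the regressor, and continuous logs allow any window.
- A reader might infer that question 2 is the only analysis linking Ned to outcomes. Question 1 is expressly about the effect of Ned and carries the pre-post comparison. Question 2 is the listed analysis that relates the amount of a patient's use to outcome.
- A reader might infer that bias is certain. It arises only if use is related to baseline health, to its course, or to another cause of outcome such as belief.

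**Conclusion.** The point holds in a limited form. As stated, question 2 is an unadjusted regression of outcome change on self-selected use, with no required time order, and its result cannot be read as benefit or harm from engagement. Under the assumed correlations (0.2 to 0.3 of use with baseline, 0.5 of baseline with 12 months), a null effect yields r of about -0.10 to -0.15 and a significant result 43% to 77% of the time at n = 320. With a baseline to 12-month correlation of 0.8 the range falls to about 20% to 40%. None of these correlations comes from the article. The sign depends on whether healthier or sicker men use the app more, and confounding of the two kinds can also cancel. The weakness is worth correcting because the remedy is cheap, but it does not affect the sample size or question 1.

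**What to change.** Restate question 2 as a landmark model: the follow-up score regressed on use logged before that assessment, for example use to month 6 predicting the 12-month score. Adjust for the baseline score of the same outcome, treatment group, age and baseline credibility/expectancy. Add a sensitivity analysis that also adjusts for the score at the landmark, since use may respond to earlier changes in health. That analysis also removes any effect of use already visible at the landmark, so the two results should be shown together. Keep consented patients with zero use in the model wherever their outcomes exist. Report an association, not improvement due to use.

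The cost is a few sentences of analysis wording. Log data, outcome scores, treatment group and credibility/expectancy are already collected, and age is taken to be among the demographic items. The downside is that use after the landmark is not analysed in this model. Residual confounding and the missing outcomes of men who leave also remain and should be stated as limitations.
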